### Data management

Each patient will be registered in the database at a dedicated website (https://www.project-redcap.org) by the research team. Regular screening of the website for missing and incorrect data will be conducted by the project leader. All collected data will be accessible via the Zenodo repository (https://zenodo.org).

Additionally, all data collected will be included in the collection form.

### Ethics statement

This project was approved by the ethics and research committee of Hospital São Rafael, Salvador—Bahia, Brazil, with registration number 28134720.1.0000.0048.

Furthermore, the individual depicted in Fig 1 has provided written informed consent (as outlined in the PLOS consent form) to publish their image alongside the manuscript.

### Confidentiality

All patients will be identified solely by a unique number assigned to them. Trial personnel are strictly prohibited from disclosing patients’ names outside the local hospital or in any study-related documents. Patients will never be identified by their names; only their assigned numbers will be used for identification purposes. The subject identification code will be securely safeguarded by the principal investigator.

## Statistical methods: Outcomes

Data will be assessed for normality using the Kolmogorov–Smirnov test. Categorical variables will be compared using the Fisher exact test or chi-square test, as appropriate, and the Student t-test or the Mann–Whitney U-test will be used to compare continuous variables, as appropriate The results will be expressed as the average and standard deviation for normally distributed data, or as the median and interquartile ranges (IQRs) for non-normally distributed data.

The primary outcome will be evaluated at T0 (basal), T1 (65 mmHg), T2 (75 mmHg), and T3 (85 mmHg) using a two-way repeated-measures ANOVA. Due to the longitudinal study design and the dependence between repeated measures, mixed-effects regression models will be considered to develop a model with different pressure targets. Each component of cerebral hemodynamics (ARI, RAP, CrCP, and P1/P2) will be assessed individually. At the 65 mmHg MAP target, cerebral hemodynamics will be evaluated by mean and IQRs.

All secondary outcomes will be exploratory and analyzed using independent samples t-tests, and chi-square test, as appropriate, without additional adjustment. Linear regression, Pearson’s correlation coefficient or Sperman coefficient will be used to test for association between cerebral parameters and organ dysfunction. Statistical analyses will be performed using the last version of SPSS for Windows (Chicago, USA). A p-value<0.05 will be considered statistically significant.

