## Methods: Participants, interventions, and outcomes

### Study setting

This single-center clinical trial, a non-randomized study, will be conducted in three intensive care units (ICUs) at Hospital São Rafael, Brazil. A screening by a multidisciplinary team will be carried out daily to identify candidates successively for inclusion, and then the inclusion and exclusion criteria will be applied.

Data collection is expected to take one year and to include at least 40 patients. Measurements will be performed using Transcranial Doppler (TCD; DWL Doppler box, Germany, Serial number: DB-1964) with a 2 MHz probe, B4C (Brain4care Corp., São Carlos, Brazil), and capturing data from the multiparametric monitor (Fig 1). Clinical and laboratory data will be collected from all subjects.

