### Sample size

This pilot project is designed to elucidate the physiological changes correlated with different blood pressure targets within cerebral hemodynamics. The insights gained will facilitate the determination of sample sizes for subsequent studies following this protocol.

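### The only normality check named, Kolmogorov–Smirnov, is weak for skewed data at about 40 patients, and the Pearson/Spearman choice has no rule; both are better fixed in advance for lactate and vasopressor dose

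*Protocol article*

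**What the plan says.** All the analysis statements are in the protocol article under Statistical methods: Outcomes.

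- Normality check: "Data will be assessed for normality using the Kolmogorov–Smirnov test". No correction for an estimated mean and SD is mentioned, and no second check.
- Summaries: "The results will be expressed as the average and standard deviation for normally distributed data, or as the median and interquartile ranges (IQRs") otherwise. This is the one place where normality is expressly made the deciding criterion.
- Two-group comparisons: "the Student t-test or the Mann–Whitney U-test will be used to compare continuous variables, as appropriate". The criterion for what is appropriate is not spelled out.
- Associations with severity markers: "Linear regression, Pearson’s correlation coefficient or Sperman coefficient will be used to test for association between cerebral parameters and organ dysfunction". No rule says which coefficient applies when.
- Significance level: "A p-value<0.05 will be considered statistically significant".

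Under Study setting: "Data collection is expected to take one year and to include at least 40 patients". Under Sample size, the study is called a pilot, and "The insights gained will facilitate the determination of sample sizes for subsequent studies following this protocol". Under Study outcome, the severity markers include lactate, vasoactive drug use, the SOFA score and delirium.

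**The concern.** The Kolmogorov–Smirnov test compares the sample with a fully specified distribution. When the mean and SD are estimated from the same sample and the standard critical values are kept, the test hardly ever rejects. The Lilliefors correction repairs its size, but the test stays less sensitive to skewness than Shapiro–Wilk. With about 40 patients, a marker with a long right tail can pass as normal and be reported as mean and SD.

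Two things are at stake. The first is description: later studies are to be planned from these data, and a mean and SD of a skewed variable is a poor planning input. The second is pre-specification: with two correlation coefficients on offer and no rule, the analyst can choose after seeing both.

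**Working it through.** The protocol gives no figure on this point, so there is none to reproduce. The check is how often each test recognises skewed data at the planned size.

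**Inputs.** From the protocol: n = 40 (the stated minimum) and alpha = 0.05. The protocol sets alpha for its analyses in general; applying it to the normality test is an assumption. Also assumed, because the protocol gives no distributions: log-normal markers with log-SD from 0.3 to 1.0. Their skewness is (exp(s²) + 2) × √(exp(s²) − 1), which is 1.75 at s = 0.5.

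**Statistic.** D = max |Fₙ(x) − Φ((x − mean)/SD)|, with mean and SD taken from the sample. At n = 40 the 5% critical value is 0.2101 from the plain table and 0.138 with the Lilliefors correction (simulated from 100,000 normal samples). There were 20,000 samples per case for D and 3,000 for Shapiro–Wilk. The Monte Carlo standard error is about √(0.61 × 0.39/20,000) = 0.3 points and √(0.85 × 0.15/3,000) = 0.7 points respectively.

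**Share of samples in which normality is rejected, n = 40**

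| Distribution | K–S, uncorrected | K–S, Lilliefors | Shapiro–Wilk |
|---|---|---|---|
| Normal | 0% | 5% | 6% |
| Log-SD 0.3 | 1% | 28% | 47% |
| Log-SD 0.4 | 3% | 44% | 70% |
| Log-SD 0.5 | 7% | 61% | 85% |
| Log-SD 0.7 | 26% | 86% | 98% |
| Log-SD 1.0 | 65% | 98% | 99.9% |

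If normality were judged within two groups of 20 (an assumed even split), the row for log-SD 0.5 becomes 1.5%, 34% and 50%.

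**What a wrong summary looks like.** Take log-SD 0.5 and median 1. The mean is exp(0.125) = 1.13 and the SD is 1.13 × √(exp(0.25) − 1) = 0.60. The mean lies 13% above the median, and mean − 2 SD = 1.13 − 1.20 = −0.07, an impossible value for a concentration or a dose. The true IQR is 0.71 to 1.40.

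**Effect on inference.** With log-SD 0.5 to 1.0 and no true effect, the t-test rejects in 4.0% to 4.8% of samples (20 v 20 and 10 v 30), and Pearson in 4.7% to 5.2% (n = 40). So there is no inflation.

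For power, take a latent correlation of 0.4 between the log marker and a normal cerebral parameter. If Pearson were always used, its power against Spearman's would be about 67% v 69% at log-SD 0.6, 64% v 69% at 0.8 and 58% v 69% at 1.0. If uncorrected K–S chose the coefficient (Spearman when normality is rejected, Pearson otherwise), power would be about 66% against 69% at log-SD 0.8, and the same at 1.0. The loss does not grow further because the test detects the stronger skew more often. With the Lilliefors correction the loss is under 1 point at both.

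**The case against.** The strongest defence is that the text gives this test little to decide. Normality is expressly tied only to the form of the summary. The two-group test is left to judgement, the correlation has no rule at all, and the secondary outcomes are labelled exploratory. That stands, and it limits the point.

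A reader might infer more in four ways, none of which the document supports:

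- **That the test sends lactate and dose to Pearson.** No sentence links the normality result to the choice of coefficient. What can be criticised is the absence of a rule.
- **That the test misses most skewed data.** This holds for the uncorrected version up to a log-SD of about 0.8. With the Lilliefors correction it holds only for mild skew, at log-SD of about 0.4 or below. The protocol does not say which version will be run.
- **That a bounded ARI will wrongly pass as normal.** A mid-scale ARI is close to normal, so not rejecting it is no error. For one set of ARI-like values truncated at 0 to 9, Shapiro–Wilk itself rejected in only 22% of samples. As a primary outcome, ARI goes to repeated-measures ANOVA or a mixed model whatever the test shows.
- **That the primary model is left unchecked.** Residual diagnostics are commonly left to a statistical analysis plan or full protocol, and neither is shown. Their absence from an article is not a defect.

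It is also fair to say that swapping one normality pre-test for another gains little alone. That is why fixing the method by variable matters more than the swap.

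**Conclusion.** The point holds in a limited form and is minor. The protocol names one normality check, makes it decide how continuous data are summarised, and picks a test that is weaker than Shapiro–Wilk on skewed data at about 40 patients, whichever variant is used. The gap at log-SD 0.5 is 85 − 61 = 24 points with the correction and 85 − 7 = 78 points without it. The practical result is that moderately skewed markers may be reported as mean and SD in a study meant to feed later sample-size calculations, and that Pearson or Spearman can be chosen after the data are seen.

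The harm to inference is small: type I error stays near 5%, and the loss of power is at most about 3 points even on the unfavourable assumption that uncorrected K–S picks the coefficient. All these sizes rest on assumed log-normal shapes and n = 40. The protocol gives no distribution for lactate or dose, and 40 is a floor. More patients would raise detection by every test.

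**What to change.** Replace the normality sentence with one stating that distributional shape is judged by Q-Q plots together with the Shapiro–Wilk test. Add a second sentence stating that lactate and vasopressor dose are summarised by median and IQR, and correlated with the cerebral parameters by Spearman's coefficient (or analysed on the log scale, with one of the two named in advance), whatever the test shows. For the other severity markers, name the coefficient for each in the same place, so that none is chosen after the data are seen.

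The cost is one or two sentences. No new data, extra patients or change to the primary analysis are needed.

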## Objectives

Our primary endpoint is to evaluate the effect of various mean arterial pressure (MAP) targets on cerebral hemodynamics (ARI, CrCP, RAP, and P2/P1) in patients with septic shock. Our secondary endpoint is to assess cerebral hemodynamics at 65 mmHg and its correlation with indicators of clinical severity and neurological dysfunction.

We hypothesize that these results will present a different pattern in patients with impaired dCA and altered ICC and consider whether these parameters can be modified by different MAP levels, suggesting a personalized approach to cerebral hemodynamics.

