### Study outcome

The primary endpoint is to assess the impact of different MAP targets on cerebral hemodynamics (ARI, CrCP, RAP by TCD, and P2/P1 by B4C) in patients with septic shock.

Secondary objectives: (1) Evaluate the effects of targeting a MAP of 65 mmHg on cerebral hemodynamics in patients with septic shock. (2) Evaluate the correlation between ARI and B4C. (3) Correlate criteria of clinical severity and neurological dysfunction with cerebral hemodynamics (This will involve assessing the correlation between markers of organ dysfunction such as lactate levels, usage of vasoactive drugs, Sequential Organ Failure Assessment (SOFA) score, and delirium with CA). (4) Assess 28-day mortality.

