CA assessment by TCD will use a 2 MHz probe, supported by a helmet frame, the middle cerebral artery will be located through the window of the temporal bone, then it will be confirmed by depth and waveform, and one of the sides will be chosen and will be kept during the protocol. All hemodynamic parameters will be collected simultaneously and transmitted to the Doppler Box through a cable connected to the multiparameter monitor. A B4C sensor will be placed on the contralateral temporal window, which consists of a monitor that quantifies local cranial bone deformations using strain-gauge sensors. The system will be positioned on the frontotemporal region, approximately 3 cm over the first third of the orbitomeatal line, and the software will indicate the wave quality generated. The measurement of ICC will be done using the curve generated by B4C, and P2/P1 > 1 will be considered altered. The quality of measurements will be closely monitored during the duration of recordings to ascertain their acceptability for subsequent stages of off-line analysis.

The instantaneous relationship between arterial blood pressure and CBv will be used to estimate CrCP and RAP for each cardiac cycle using the first harmonic method [18]. Beat-to-beat data will be spline interpolated and resampled at 5 Hz to produce signals with a uniform time base.

Dynamic CA will be assessed using transfer function analysis, using spontaneous fluctuations of MAP as input and corresponding changes in CBv as output in recordings for each MAP target (lasting 5 min), as described previously [19,20]. The Welch method will be adopted for smoothing spectral estimates obtained with the fast Fourier transform (102.4 s segments, 50% superposition) leading to frequency-dependent estimates of coherence, gain and phase. Using the inverse fast Fourier transform, the CBv response to a step change in MAP will also be derived and compared with ten template curves proposed by Tiecks et al. [21] to estimate the ARI [22,23] Baseline cerebral hemodynamic parameters will be reported as the average over a 5-min recording at rest. Values of ARI < 4 will characterize impaired dCA.

The protocol will be interrupted if at any time during the data collection any of the adverse effects, described below, are identified.

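### Four unranked primary outcomes are each tested at 0.05 with no multiplicity rule, and the analysis section names one of them as its reciprocal

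*Protocol article*

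**What the plan says.** All references are to the protocol article.

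- **Objectives:** "Our primary endpoint is to evaluate the effect of various mean arterial pressure (MAP) targets on cerebral hemodynamics (ARI, CrCP, RAP, and P2/P1"). The four measures stand side by side and none comes first.
- **Study outcome:** the same four again, as one endpoint: "The primary endpoint is to assess the impact of different MAP targets on cerebral hemodynamics (ARI, CrCP, RAP by TCD, and P2/P1 by B4C").
- **Statistical methods: Outcomes, test:** the primary outcome is compared across baseline and the three targets, ending "75 mmHg), and T3 (85 mmHg) using a two-way repeated-measures ANOVA". Mixed-effects models are also to be considered.
- **Statistical methods: Outcomes, components:** "Each component of cerebral hemodynamics (ARI, RAP, CrCP, and P1/P2) will be assessed individually".
- **Statistical methods: Outcomes, threshold:** "A p-value<0.05 will be considered statistically significant".
- **Statistical methods: Outcomes, multiplicity:** the only statement concerns the secondary outcomes: "All secondary outcomes will be exploratory and analyzed using independent samples t-tests, and chi-square test, as appropriate, without additional adjustment".
- **Methods: Data collection and management:** the ratio and its cut-off are defined as "P2/P1 > 1 will be considered altered".
- **Study setting:** "Data collection is expected to take one year and to include at least 40 patients".

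The Introduction, Sample size and Interim analysis sections call the study a pilot.

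**The concern.** There are two separate faults in the same sentence of the statistical section.

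**Multiplicity.** The section fixes the test, the separate assessment of each component and the threshold. It deals with multiplicity for the secondary outcomes by calling them exploratory and leaving them unadjusted. By contrast, the four primary components read as inferential, yet no hierarchy, composite, all-must-succeed requirement or adjustment is given. A report could therefore rest a statement that MAP target alters cerebral hemodynamics on whichever component crossed 0.05, and that statement would not carry a 5% error rate. Because the results are meant to inform the sample size of later studies, picking the significant component would also pass on an effect that is too large on average.

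**Ratio.** The section that governs the analysis names the inverse of the outcome declared elsewhere. An analyst who followed it literally would report effects in the opposite direction and could not apply the cut-off of 1 as defined.

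**Working it through.** **Inputs**

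- Number of primary components: 4 (Objectives; Study outcome).
- Threshold per test: 0.05 (Statistical methods: Outcomes).
- Conditions per component: 4, T0 to T3 (same section).
- Patients: 40, the stated minimum (Study setting).
- Correlation between the four outcomes: not given, so assumed over 0 to 0.9.

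The article states no family-wise error, so there is no figure of its own to reproduce. The 0.05 is a chosen input.

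**Step 1. Independent outcomes, all four nulls true**

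P(at least one p<0.05) = 1 − (1 − 0.05)^4 = 1 − 0.8145 = 0.1855, or 18.5%.

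**Step 2. Upper bound under any dependence**

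4 × 0.05 = 0.20, or 20%.

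**Step 3. Correlated outcomes**

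For each correlation, 20,000 null trials were simulated with 40 patients, four conditions and four equally correlated outcomes. Each outcome was tested by a repeated-measures ANOVA on the MAP condition, with sphericity assumed. The last column tests each component at 0.05/4 = 0.0125. When all four nulls are true, Holm has the same family-wise error as this Bonferroni rule, because both reject something only if the smallest p-value is below 0.0125.

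| Assumed correlation | At least one p<0.05 | At least one p<0.0125 |
|---|---|---|
| 0 | 18.2% | 4.9% |
| 0.3 | 17.7% | 4.8% |
| 0.5 | 15.9% | 4.4% |
| 0.7 | 13.1% | 3.9% |
| 0.9 | 9.7% | 2.6% |

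The first row agrees with Step 1 within simulation error. Exact value for the last column with independent outcomes: 1 − (1 − 0.0125)^4 = 0.0491.

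**Step 4. The ratio, section by section**

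| Section | Ratio named |
|---|---|
| Abstract, Methods | P2/P1 |
| Objectives | P2/P1 |
| Study outcome | P2/P1 |
| Table 2 | P2/P1 |
| Data collection and management | P2/P1, altered if > 1 |
| Statistical methods: Outcomes | P1/P2 |

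A two-value illustration (invented values) shows that the two forms are not interchangeable:

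- P2/P1 of 0.6 and 1.5 has mean (0.6 + 1.5)/2 = 1.05, above the cut-off of 1.
- The reciprocals are 1.667 and 0.667, with mean 1.167. Turned back, 1/1.167 = 0.857, below the cut-off.

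The two summaries fall on opposite sides of 1. An ANOVA compares such means, so it is not the same analysis on the two scales. The swap adds no test, however, and leaves the figures in Steps 1 to 3 unchanged.

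**The case against.** **No decision rule is stated.** The protocol nowhere says that one significant component makes the study positive. Assessing each component individually can be read as four separate statements, each with its own 5% error. This stands, and it makes the 10% to 20% conditional. But the protocol does not exclude the at-least-one reading either, and it puts all four under a single endpoint.

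**It is a pilot.** The purpose is physiological description and planning of later studies, which lowers the consequence of a false positive. This also stands. It is a reason to label the primary analysis exploratory, which the text does only for the secondary outcomes.

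**A reader might infer that a false-positive primary result is likely.** The figures do not support that. The planned tests give 10% to 20%, and about 14 independent tests at 0.05 would be needed to pass 50% (ln 0.5 / ln 0.95 = 13.5).

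**A reader might infer an error near 60%.** All six pairwise comparisons of T0 to T3 per outcome, tested without adjustment and regardless of the omnibus result, do give 59.7% in simulation with independent outcomes. The protocol specifies no such comparisons, and post-hoc procedure is ordinary detail for a statistical analysis plan. If they followed only a significant omnibus test, the figure would return to about 18%.

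**A reader might link the reciprocal to the false positives.** It has no bearing on them. P1/P2 appears once against five uses of P2/P1, so it is most probably a slip, and the sentence containing it applies no cut-off. It still needs correcting, because it sits in the section that an analyst would follow.

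**Conclusion.** The concern holds in limited form. Four co-listed primary outcomes are each tested at 0.05 with no rule for combining them. If any single significant component were taken as a positive primary result, the family-wise error would be 18.5% with independent outcomes, at most 20%, about 16% at correlation 0.5 and about 10% at 0.9. That is roughly two to four times the nominal 5%.

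The figures rest on three assumptions: all four null hypotheses are true, the at-least-one reading is used (the protocol states no rule either way), and the correlation lies in the assumed range. The upper bound of 20% does not depend on the correlation.

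The P1/P2 label is a separate inconsistency within the article, probably clerical. It reverses direction and changes the means and the ANOVA if followed literally.

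**What to change.** In Statistical methods: Outcomes, make two changes.

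1. **State how the four primary components are handled**, by one of two routes:
   - Apply Holm across the four omnibus tests of MAP target. The ordered p-values are compared with 0.05/4 = 0.0125, 0.05/3 = 0.0167, 0.05/2 = 0.025 and 0.05, stopping at the first that fails. This holds the family-wise error at 5% or less whatever the correlation.
   - Or state that all four are exploratory, and report differences between targets as estimates with confidence intervals and no confirmatory claim. This suits the pilot purpose.
2. **Replace P1/P2 with P2/P1**, to match the declared outcome and its cut-off.

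Making ARI the sole primary outcome with a linear MAP slope would also control the error, but the fault does not require it. It would demote the only measure of intracranial compliance and could miss a non-monotone pattern. That is a scientific choice for the investigators.

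**Cost.** Holm costs slightly less power per component, and the exploratory label gives a weaker claim. Either is a sentence or two of text and needs no new data. If the status of the primary endpoint changes, the article's own rule on communicating relevant modifications to the Ethics Committee and the registry applies. The ratio correction is a change of label only.

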## Methods: Data collection and management

Data collection on admission will include the following: demographic characteristics, comorbidities, source of infection, Sequential Organ Failure Assessment at ICU admission, temperature, hemogram lactate, hepatic and renal markers, Glasgow Coma scale or Richmond Agitation Sedation Scale, Confusion Assessment Method for the ICU scale, drug for sedation, neuromuscular blocking agents, mechanical ventilation, quantify vasoactive drug dose on collection day, arterial blood gasses before and after the protocol, presence of acute cardiac dysfunction by echocardiography and left ventricle ejection fraction. We will describe the utilization of antipsychotics or sleep-improving medications before ICU admission.

At the time of data collection, the presence of brain dysfunction associated with sepsis will be assessed by: a Glasgow scale score < 15 or when disorientation, disorganized thinking, or agitation are reported by the attending physician, regardless of sedative/analgesic use and in the absence of neurological disease (i.e., dementia, cerebrovascular disease, brain tumors, previous traumatic brain injury). Data from medical records will be used to access such information, the description of the change in the level of consciousness or the use of antipsychotics or dexmedetomidine will be interpreted as a brain dysfunction.

Systemic physiological monitoring will be performed by an arterial line, cardioscopy, pulse oximetry, and capnography (if unavailable at the time of collection, this will be described). Before starting the monitoring, the proper functioning of the arterial line will be confirmed and the site described.

Each patient will adhere to a uniform protocol where, after establishing baseline measures, the mean arterial pressure (MAP) targets will be sequentially increased in the order of 65, 75, and then 85 mmHg. This structured approach ensures sample homogeneity.

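### The blanket independent-samples rule for secondary outcomes does not fit a within-patient comparison of 65 mmHg with another pressure, nor the ARI versus P2/P1 correlation

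*Protocol article*

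**What the plan says.** Statistical methods: Outcomes gives one rule for the secondary outcomes: "All secondary outcomes will be exploratory and analyzed using independent samples t-tests, and chi-square test, as appropriate, without additional adjustment". The significance rule is "A p-value<0.05 will be considered statistically significant".

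Two of the four secondary objectives under Study outcome matter here:

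- Objective 1: "Evaluate the effects of targeting a MAP of 65 mmHg on cerebral hemodynamics in patients with septic shock". No comparator is named.
- Objective 2: "Evaluate the correlation between ARI and B4C". Neither the reading nor the method is named.

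The design is within-patient. Under Methods: Data collection and management, after baseline, "the mean arterial pressure (MAP) targets will be sequentially increased in the order of 65, 75, and then 85 mmHg". Each patient can therefore contribute four readings. On numbers, Study setting says: "Data collection is expected to take one year and to include at least 40 patients".

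Three other statements in the statistical section bear on the point:

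- For the guideline target there is a descriptive sentence: "At the 65 mmHg MAP target, cerebral hemodynamics will be evaluated by mean and IQRs".
- The primary outcome is evaluated at T0 to T3 "using a two-way repeated-measures ANOVA", with mixed-effects models to be considered because readings within a patient are dependent.
- Linear regression, Pearson and Spearman are assigned to the association of cerebral parameters with organ dysfunction. ARI against P2/P1 is not mentioned there.

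**The concern.** The section recognises dependence between readings for the primary outcome, then prescribes tests that assume independent groups for all secondary outcomes. The tests named in the section (t, Mann-Whitney, Fisher, chi-square) include no signed-rank or McNemar test, and no paired t-test by name.

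For objective 1 the secondary-outcome text offers two routes. A summary at 65 mmHg alone describes patients at that pressure but cannot show an effect of it. An independent-samples test of 65 mmHg against another pressure leaves the between-patient variation in the standard error, although each patient is their own control. The error is conservative: confidence intervals too wide and real changes missed, rather than false claims.

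For objective 2, read literally, the rule assigns a t-test or chi-square test to a question about the correlation of two continuous measures. Neither estimates a correlation.

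The Sample size section says that this pilot will inform the size of later studies. For a within-patient design that requires the mean and SD of the within-patient difference, which an independent-samples analysis does not give.

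**Working it through.** **Inputs from the protocol article:** n = 40 (the stated minimum); four readings per patient; alpha 0.05, taken as two-sided because sidedness is not stated. The article gives no power calculation, effect size, SD or within-patient correlation, so there is no figure to reproduce.

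**Assumed, shown as ranges:** true difference d between two pressures, in between-patient SD units, of 0.3 or 0.5; within-patient correlation rho from 0.3 to 0.8; equal SDs at the two pressures.

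**1. Standard error.** The independent test uses SD × sqrt(2/n). The true standard error of the mean difference is SD × sqrt(2(1-rho)/n). The ratio is 1/sqrt(1-rho):

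- rho 0.3: 1/sqrt(0.7) = 1.20
- rho 0.5: 1/sqrt(0.5) = 1.41
- rho 0.7: 1/sqrt(0.3) = 1.83
- rho 0.8: 1/sqrt(0.2) = 2.24

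**2. Type I error of the independent test on paired data** (40,000 simulations, nominal 5%): 2.1% at rho 0.3, 0.6% at rho 0.5, about 0% at rho 0.7 and above.

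**3. Power.** For the paired t-test the noncentrality is d × sqrt(n)/sqrt(2(1-rho)) on 39 degrees of freedom. At d = 0.5 and rho = 0.5 this is 0.5 × 6.32/1 = 3.16, giving power 0.87. The paired figures agreed with simulation. The independent figures are simulated.

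| d | rho | paired | independent | share of power lost |
|---|---|---|---|---|
| 0.5 | 0.3 | 0.74 | 0.62 | 17% |
| 0.5 | 0.5 | 0.87 | 0.64 | 26% |
| 0.5 | 0.7 | 0.98 | 0.67 | 31% |
| 0.5 | 0.8 | 1.00 | 0.70 | 30% |
| 0.3 | 0.3 | 0.35 | 0.23 | 35% |
| 0.3 | 0.5 | 0.46 | 0.19 | 59% |
| 0.3 | 0.7 | 0.67 | 0.14 | 80% |
| 0.3 | 0.8 | 0.83 | 0.09 | 89% |

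The last column is (paired - independent)/paired, computed before rounding and accurate to about one percentage point.

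**4. ARI against P2/P1.** The article does not say which readings enter. Suppose k readings per patient were pooled and treated as independent, with no true association and the same intraclass correlation (ICC) in both measures. The variance of the correlation is then inflated by about 1 + (k-1) × ICC². For k = 4 and ICC = 0.5 this is 1 + 3 × 0.25 = 1.75, so the approximate type I error is 2 × (1 - Phi(1.96/sqrt(1.75))) = 13.8%. Simulation (20,000 replicates) gives:

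| ICC | 3 readings | 4 readings |
|---|---|---|
| 0 | 5.1% | 5.0% |
| 0.3 | 7.2% | 7.9% |
| 0.5 | 11.1% | 13.7% |
| 0.7 | 16.7% | 21.5% |
| 0.9 | 23.0% | 29.6% |

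With one pair per patient the error stays at the nominal 5%.

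**The case against.** The best defence is that the 65 mmHg question does not depend on the independent test. It has its own descriptive sentence, and the specific sentence can be read as governing over the general one. The Abstract and Objectives also word the aim as assessing hemodynamics at 65 mmHg, which is descriptive. Moreover, T0 and T1 are two levels of the primary repeated-measures analysis, which respects the pairing. Much of this stands: a reader who infers that the within-patient comparison is nowhere handled properly would be wrong. What remains is that Study outcome speaks of effects, no T1-T0 contrast is named, and the only tests assigned to secondary outcomes are for independent groups.

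A reader might also infer that most of the power is lost. That is not a general result. At d = 0.5 the loss is between a sixth and just under a third. It exceeds half only for smaller effects with substantial within-patient correlation (at d = 0.3, from rho of about 0.5). The article gives no values to choose between these cases.

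A third inference, that the ARI versus P2/P1 correlation would be falsely significant, assumes pooling of readings across targets. Nothing in the article says so.

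Finally, the outcomes are labelled exploratory, the tests are to be chosen as suits the data, and independent-samples tests are right for between-patient items such as delirium or 28-day mortality. These points lower the severity. The latitude in choosing tests helps only partly, because no paired option is named among them.

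**Conclusion.** The point holds in limited form. As a rule for all secondary outcomes, independent-samples t-tests and chi-square tests do not fit a within-patient comparison of 65 mmHg with another pressure and do not answer the ARI versus P2/P1 question.

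If the rule were applied to objective 1 with 40 patients, standard errors would be about 1.2 to 2.2 times too large for rho 0.3 to 0.8, and the test would be strongly conservative. The power cost rests on assumed effect sizes and correlations and ranges from modest to large.

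For objective 2 the defect is an unfixed method. A type I error of roughly 7 to 30% (ICC 0.3 to 0.9) would follow only from naive pooling, which is not a stated plan.

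Because the outcomes are exploratory, the study is a pilot and the primary model already handles dependence, the severity is minor to moderate.

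**What to change.** Replace the blanket sentence with a short paragraph:

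- **Between-patient comparisons** (for example delirium yes/no, 28-day mortality): keep the independent-samples and chi-square or Fisher tests.
- **Objective 1:** report the T1-T0 within-patient difference for each parameter with a 95% confidence interval, as a contrast from the repeated-measures or mixed model already planned, or from a paired test. For a change in the proportion with ARI < 4 or P2/P1 > 1, use McNemar's test. Keep the summary at 65 mmHg as description. If only description is intended, reword the objective so that it does not promise an effect.
- **Objective 2:** name a correlation coefficient on one ARI and P2/P1 pair per patient at a stated target, or a repeated-measures correlation if several readings are used.

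The cost is one paragraph of text. No new data, patients or measurements are needed, and the SD of the within-patient difference becomes available for sizing later studies.
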